# Community-based aftercare following an emergency department presentation for attempted suicide or high risk for suicide: study protocol for a non-randomised controlled trial

**DOI:** 10.1186/s12889-019-7751-8

**Published:** 2019-10-26

**Keywords:** Suicide prevention, Aftercare, Peer worker

## Abstract

**Background:**

Suicide is a major public health issue worldwide. Those who have made a recent suicide attempt are at high risk for dying by suicide in the future, particularly during the period immediately following departure from a hospital emergency department. As such the transition from hospital-based care to the community is an important area of focus in the attempt to reduce suicide rates. There is a need for evaluation studies to test the effectiveness of interventions directed to this stage (termed ‘aftercare’ interventions).

**Methods:**

A controlled non-randomised two group (intervention vs treatment-as-usual control) design, using an intention-to-treat model, will evaluate the effectiveness of a suicide prevention aftercare intervention providing follow-up after presentations to a hospital emergency department as a result of a suicide attempt or high risk for suicide. The intervention is a community-based service, utilising two meetings with a mental health clinician and follow-up contacts by peer workers via a combination of face-to-face and telephone for four weeks, with the option of extension to 12 weeks. Seventy-five participants of the intervention service will be recruited to the study and compared to 1265 treatment-as-usual controls. The primary hypotheses are that over 12 months, those who participate in the aftercare follow-up intervention are less likely than controls to present to a hospital emergency department for a repeat suicide attempt or because of high risk for suicide, will have fewer re-presentations during this period and will have lower all-cause mortality. As a secondary aim, the impact of the intervention on suicide risk factors for those who participate in the service will be evaluated using pre- and post-intervention repeated measures of depression, anxiety, stress, hopelessness, belongingness, burdensomeness, and psychological distress. Enrolments into the study commenced on 1 November 2017 and are anticipated to cease in November 2019.

**Discussion:**

The study aims to contribute to the understanding of effective interventions for individuals who have presented to a hospital emergency department as a result of a suicide attempt or at high risk for suicide and provide evidence in relation to interventions that incorporate peer-workers.

**Trial registration:**

ACTRN12618001701213. Registered on 16 October 2018. Retrospectively registered.

## Background

Suicide is a major public health issue worldwide [1]. In Australia, 3128 people died by suicide in 2017 (12.7 per 100,000), with suicide the leading cause of death amongst 15–44 year olds [2]. When it comes to suicidal behaviours more broadly, deaths are considered ‘the tip of the iceberg’ [3], with estimates of approximately 30 suicide attempts for every one suicide death [4]. Those who have made a recent suicide attempt are at high risk for dying by suicide in the future [5, 6], particularly immediately after discharge from a hospital emergency department [7] and within the first year following a suicide attempt [5, 8].

The most common point of contact that people who have attempted suicide have with support services is via a hospital emergency department [9]. However, people who have presented to an emergency department following a suicide attempt have described the support received as either insufficient [9] or completely absent [10–13]. As a result, there have been numerous calls to improve the support people receive within emergency departments and improve the way they are connected with ongoing community-based care [14, 15].

In the context of physical health care, the quality of the discharge planning and transfer of care is known to have significant impacts on patient outcomes [16–21]. Therefore, improved transition from hospital-based care to community supports for people presenting to an emergency department following a suicide attempt is a priority for effective suicide prevention [14, 15]. This type of intervention is referred to as ‘aftercare’.

Aftercare is consistently included as a key component of multilevel initiatives, or a ‘systems approach’ to suicide prevention [22–26]. One such systems approach is the *LifeSpan* project [23], which is being coordinated by the Black Dog Institute and implemented within four regions of New South Wales, Australia, including the Illawarra Shoalhaven region. The *LifeSpan* project involves implementing nine suicide prevention strategies simultaneously. Of all these strategies, implementing effective aftercare is estimated to reduce suicide attempts by 19.8%, the biggest impact from any one strategy in the *LifeSpan* systems approach [27].

The first landmark study evaluating the impact of a coordinated aftercare service was conducted on the outskirts of Oslo, Norway [28]. In what became known as ‘the Bærum Model’, people who presented to hospital after attempting suicide (but were not directly admitted) were followed up with home visits for up to 6 months and provided with support via a combination of face-to-face and phone contacts. There were four components to the support offered: (1) outreach – immediate, assertive outreach and follow-up after discharge from hospital, (2) problem-solving – solution focused counselling, (3) adherence – encouragement to remain engaged with treatment and follow recommendations, and (4) continuity – maintain contact with a consistent group of support people [29]. This intervention was credited with having contributed to a significant reduction in suicidal behaviours, from 170 per 100,000 in 1984 to 79 per 100,000 in 1995; a reduction of 53.5% [28].

These findings were supported by a Danish randomised controlled trial of a 6-month aftercare service based on the Bærum Model [30], in which 69 intervention participants were compared with 64 treatment-as-usual controls. The researchers found that significantly fewer people in the intervention group re-attempted suicide (8.7%) than the control group (21.9%) over a 12-month period. This study also found reduced numbers of repeated acts (8 in the intervention group versus 22 in the control group). The researchers noted that a key characteristic of the intervention was its “swift and rather aggressive outreach” [30] p.296, as well as the capacity to adapt the support to account for personal factors. A 5-year follow-up study found the number of people with repeated suicide attempts remained lower for the intervention group for up to 3–4 years, and the total number of repeat suicide attempts remained lower for the intervention group after 5 years [31].

Fundamentally, aftercare interventions aim to bridge the transition between an emergency department and community-based supports, with the key factor being a focus on making and keeping contact to ensure a constant sense of connectedness [31, 32]. As such, aftercare can be delivered via a number of methods – face-to-face contact [29], phone contact only [33, 34], a combination of phone and face-to-face [35], or mailed out letters [36–39]. The aftercare models evaluated have also ranged in duration, from a single contact [40] to regular contacts over 18 months [35]. Each of these models have illustrated the potential for aftercare services to have an impact on suicidal behaviours for those who have attempted suicide.

### Peer workers

Aftercare services have also varied in terms of their staffing profile, typically using a combination of doctors, nurses, psychologists, community workers, and social workers [41]. However, there are no records in the literature of aftercare services utilising *peer workers*; people employed on the basis of their personal lived experience of suicide or mental illness and recovery [42]. There is a growing body of evidence to support the use of peer workers in assisting people who are experiencing mental illness [42]. A review of four randomised controlled trials by Davidson, Chinman, Sells and Rowe [43] found that, across most outcomes, peer workers were just as effective as professionals in providing case management and support for individuals with severe mental illness. Furthermore, one of the studies reviewed found significantly fewer hospitalisations for those who were being case managed by peer workers compared to those being managed by a mental health professional [44]. Similarly, a reduction in the number of hospital re-admissions over a three-year period for mental health patients who received peer support has been observed [45]. These findings suggest there are potential benefits to involving peer workers in mental health care, although thus far, the majority of studies have been qualitative in nature and the few randomised controlled trials that have been conducted have primarily focussed on case management interventions [43, 46, 47]. A literature search conducted by the authors did not produce any studies that had specifically focussed on the use of peer workers with suicidal clients or in the context of aftercare services. As a result, there is a need for research to explore the effectiveness of a suicide prevention intervention utilising peer workers.

### GROW coaching model

In addition to providing a bridge between crisis (hospital-based) care and ongoing (community-based) care, the Bærum aftercare model also emphasised the importance of a practical problem-solving approach. An example of such an approach is provided by the GROW coaching model (Goal, Reality, Options, Wrap-up). The GROW model is a simple, collaborative, solution focussed framework that informs the structure of intervention sessions with clients [48–50]. Clients are firstly asked to set a goal (G) for what they would like to achieve during the coaching session. They are encouraged to create a goal that is specific and within their control, and they are assisted in breaking down larger goals into smaller, concrete steps [51]. Secondly, clients are assisted in gaining a better understanding of their reality (R), or current situation [49, 50]. They are encouraged to consider what they have previously found helpful, what they have found to be unhelpful, and any barriers they may be experiencing regarding their goals [51]. Thirdly, clients are encouraged to evaluate different options (O) for overcoming likely barriers to achieving goals [48, 51]. The fourth stage of the GROW model is the wrap-up (W) [49, 50], which encourages clients to create specific action steps in order to move forward, overcome barriers and evaluate their progress [48]. An advantage of a practical problem-solving framework, such as the GROW model is that it can be implemented, with relatively brief training, by staff of any background, including non-professionals.

### Targeting suicidal thoughts and behaviours

A critical factor in suicide prevention interventions is to directly target suicidal thoughts and behaviours [52]. An empirically supported example is the *Collaborative Assessment and Management of Suicide* (CAMS) model [53, 54], in which a clinician and client work collaboratively through goal-setting, treatment planning and monitoring [53]. Clients are asked to; outline the key problems or ‘drivers’ that are contributing to their suicidality and then work alongside a clinician to produce a set of goals and objectives to alleviate these problems; consider alternative behaviours to self-harm that they can engage in if in a suicidal crisis (e.g., going for a walk; calling an ambulance; people they can contact for help); and rate their suicide risk factors. Clients evaluate their goals and stabilisation plan at every treatment appointment [53, 54]. The structure of the CAMS framework is maintained within treatment sessions via the application of the *Suicide Status Form* (SSF), which is a tool that guides the conversation and collaborative work between the clinician and client.

Application of the CAMS framework has been shown to reduce suicidal ideation and/or behaviours amongst college students [54, 55] and defence personnel [56], as well as both outpatients [57, 58] and inpatients [59–61]. It has been found to be effective when adapted to online learning modalities [62] and has also demonstrated efficacy when delivered by clinicians from a range of disciplines [63]. The CAMS framework has not, to the authors’ knowledge, been applied within an aftercare context.

This paper describes the study protocol for a non-randomised controlled trial of an aftercare suicide prevention intervention that will provide follow-up to people who have presented to a hospital emergency department following a suicide attempt or with significant suicide risk, and who are not admitted to hospital as an inpatient, or being actively case managed by mental health services, at that time. The intervention, known in the region as ‘Aftercare’, will utilise clinicians and peer workers, and provide practical solution-focused intervention and targeted intervention of suicidal thoughts and behaviours. The Aftercare intervention will utilise the GROW coaching model and apply the SSF from the CAMS framework to target suicidal thoughts and behaviours directly. The intervention will involve a combination of face-to-face and telephone sessions over a four-week period, with the option of extension to 12 weeks.

## Methods/design

### Study aims

The primary objectives of the study are to evaluate the impact of the Aftercare intervention on the likelihood of a re-presentation to an emergency department as a result of a suicide attempt or because of high risk for suicide, the rates of re-presentation to emergency departments as a result of one or more repeat suicide attempt(s) or because of high risk for suicide, and the number of deaths by any cause. The secondary objectives of the study are to evaluate the impact of the Aftercare intervention on factors associated with increased risk of suicide, namely, mood [64], hopelessness [65, 66], belongingness, burdensomeness [66], and psychological distress [67, 68].

It is hypothesised that;
Participants of the Aftercare intervention will be less likely to have a repeat presentation to an emergency department within 12 months as a result of a suicide attempt or being at high risk for suicide than non-participants.Participants of the Aftercare intervention will have lower rates of re-presentations to a hospital emergency department for suicide attempt or high risk for suicide within 12 months than non-participants.Participation in the Aftercare intervention will be associated with fewer all-cause deaths within 12 months than non-participation.For participants of the Aftercare intervention, depression, anxiety, stress, hopelessness, belongingness, burdensomeness, and psychological distress will be improved in comparison to baseline levels following the intervention.

### Study setting

The Aftercare intervention will be implemented in the Illawarra Shoalhaven region on the south-east coast of New South Wales (NSW), Australia. The region has a population of just over 400,000 and is served by three main public hospitals and several smaller regional hospitals [69]. The region experiences a suicide rate of 12.6 per 100,000, which is above the NSW state average of 10.6 per 100,000 [2], and more than 1000 suicide-related presentations to emergency departments each year [70].

The intervention will be implemented by a collaboration of three community-based organisations – Grand Pacific Health, Flourish Australia, and South Coast Medical Service Aboriginal Corporation. Referrals to the Aftercare service will be received by the service providers from the emergency departments of the three main hospitals.

### Study design

A controlled non-randomised two group (intervention vs treatment-as-usual (TAU) control) design will be used to test the primary hypotheses (hypotheses 1–3), following the intention-to-treat method. The secondary objectives of the study will be evaluated using a pre- and post-intervention repeated measures design (hypothesis 4), in which the intervention group (i.e. participants of the Aftercare intervention) will complete self-report questionnaires prior to their initial intervention session, and again at the time of their discharge appointment from the service.

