### Data analysis

Analyses will be conducted using the Statistical Package for the Social Sciences version 25 [85] and SAS v9.4 [86]. Primary analyses will be conducted according to the intention-to-treat approach. Presentations to an emergency department with a repeat suicide-related event and for all-cause death will be compared between the two non-randomised groups (intervention vs control) using a Kaplan Meier plot where the initial presentation to an emergency department is designated as time zero, and using censoring. A log-rank test will compare the Kaplan Meier curves of the two groups.

A negative binomial regression model will be applied to the data to estimate the effect of the intervention on re-presentation rates, accounting for varying lengths of follow-up period and adjusting for service and person-level characteristics (e.g. facility, age, sex, indigenous status) and censoring.

To investigate the impact of the service on suicide risk factors (secondary outcome measures), a comparison of pre- and post-intervention outcome measures will be conducted for participants of the intervention using paired t-tests, or a Wilcoxon signed-ranks test (if the sample is non-normally distributed), adjusting for multiple comparisons (Bonferroni correction).

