### Sample size and statistical power

The sample size required to achieve power of 80% was estimated for the primary analyses using G*Power [87]. Local hospital data (2014/2015 year) indicated that approximately 1340 people present to emergency departments with suicide-related presentations annually and systematic reviews have estimated that 16% re-attempt suicide within 12 months [5]. Based on Hvid et al.’s [30] report that an intervention group had approximately half the rate of deaths by suicide than a TAU group at 12 months (.087 vs .219), the sample size required for a log-rank test at α level .05 is 75 participants in the intervention group and 1265 participants in the control group.

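### Three primary hypotheses have no lead endpoint, order or success rule; the sample size spends the full .05 on one log-rank test, and Bonferroni is stated only for the secondary measures

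*Protocol article*

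**What the plan says.** Study aims lists three primary objectives, and Study design confirms them as the "primary hypotheses (hypotheses 1–3"). The abstract joins the same outcomes in one sentence: participants are less likely to re-present, "will have fewer re-presentations during this period and will have lower all-cause mortality".

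Data analysis compares suicide-related re-presentation and all-cause death by Kaplan-Meier curves with a log-rank test, and re-presentation rates by negative binomial regression. It gives no significance level for any of these. Its one statement on multiplicity, "adjusting for multiple comparisons (Bonferroni correction"), belongs to the sentence on the pre-post secondary measures.

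Alpha appears once, under Sample size and statistical power: "the sample size required for a log-rank test at α level .05 is 75 participants in the intervention group". The same section says "The sample size required to achieve power of 80% was estimated for the primary analyses using G*Power", in the plural, but describes one calculation, on the proportions .087 and .219.

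**The concern.** The three primary tests carry the effectiveness claim against controls. The secondary measures are before-and-after changes in one group. The article commits to multiplicity control for the second set and states none for the first, so the protection sits with the weaker evidence.

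Without a lead endpoint or success rule, a reader of the results cannot tell which pattern counts as a positive trial. One significant result out of three, two out of three, or a benefit on re-presentation alongside an uninformative mortality comparison could each be presented as support. The error rate of the trial's conclusion is then undefined, and the .05 in the sample size describes only one of the tests.

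**Working it through.** **Inputs.** From the article: three primary hypotheses; α .05; power 80%; 12-month proportions .087 and .219; 75 intervention and 1265 control participants; 16% re-attempting within 12 months. Not in the article, so assumed: two-sided tests, correlations between the test statistics, over-dispersion of counts, and 12-month mortality of 1% to 3%.

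**1. The planned sample size.** With k = 1265/75 = 16.87 and pooled proportion (75 × .087 + 1265 × .219)/1340 = .2116, the two-proportion formula is

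n = [z_α √((1 + 1/k) × .2116 × .7884) + z_β √(.087 × .913 + .219 × .781/k)]² / (.219 − .087)²

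At two-sided .05 (z_α = 1.960, z_β = 0.842): n = (.824 + .252)²/.01742 = 66.4, so 67. The continuity-corrected form, (n/4)[1 + √(1 + 2(1 + 1/k)/(n × .132))]², gives 74.2, so **75**, the planned number. One-sided .05 gives 52, or 59 corrected. The design therefore uses the full two-sided .05 on one test and reserves nothing for the other two.

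**2. What a later alpha split would cost.** At .05/3 = .0167 two-sided, the same formula gives 91, or **99** with the continuity correction, and 99 × 16.87 ≈ 1670 controls. At 75 and 1265, power falls from 85.7% to 67.6% (normal approximation, uncorrected).

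**3. At least one false significant result, either direction,** if each test is at two-sided .05 and any one suffices:

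| Assumption | Chance |
|---|---|
| Independent tests, 1 − .95³ | 14.3% |
| First two correlated 0.8 to 0.95, mortality correlated 0 to 0.2 with them | 11.0% to 12.4% |
| First two perfectly correlated | about 9.7% |
| Null simulation, 75 vs 1265, re-presentation .16 or .219, mortality 1% or 3% | 10.4% to 13.0% |

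**4. At least one false claim of benefit,** same rule, nominal .025 per test:

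- Normal theory, all three tests: 7.3% if independent (1 − .975³), falling to 4.9% if the first two are perfectly correlated.
- Normal theory, the two re-presentation tests alone, correlated 0.8 to 0.95: 3.9% to 3.2%.
- Null simulation as above: 1.7% to 3.7%. It is lower because the tests in a group of 75 run mostly below .025 on the benefit side, and mortality contributed nothing.

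**5. Mortality.** Suppose no intervention participant dies and control mortality is m. With the intervention share of those at risk held at 75/1340, the log-rank statistic is approximately √(1265m × 75/1265) = √(75m). At m = 1%, 2% and 3% this is 0.87, 1.22 and 1.50. Reaching 1.96 needs m = 1.96²/75 = 5.1%, about 65 control deaths. In the simulations at 1% and 3%, mortality never reached significant benefit.

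**The case against.** The strongest reply is that this is a condensed article. Endpoint hierarchy and alpha allocation are often left to an analysis plan, which is not shown and may settle the matter. That stands in part: nothing here shows that no rule exists anywhere. But the article is not simply silent. It addresses multiplicity, places the correction on the secondaries only, labels three hypotheses primary, and fixes the sample size at full alpha for one test. A split introduced later would conflict with that sample size (99 against 75).

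A reader might infer that the plan tests each primary at .05, so that the chance of a false effectiveness claim is about double the stated α. The article does not support this. It gives α for one log-rank test and never says that any one result suffices. The doubling also counts false signals of harm, whereas all three hypotheses are worded as benefits. On the benefit side the figure is about 3% to 7%, or less in simulation. That exceeds .025 per test in most settings, but it is not double .05.

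It can also be said that the abstract's wording implies all three must succeed, in which case error is at most .05. That rule is not stated either. At assumed mortality of 1% to 3% it could hardly be met, because even zero intervention deaths would not give a significant difference at the expected number of control deaths.

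**Conclusion.** The point holds in a conditional form. The article fixes three primary hypotheses without a lead endpoint, order or success rule, sizes the trial on one of them at full .05, and states a correction only for the secondaries.

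If each primary is tested at two-sided .05 and any one suffices, at least one false significant result has a chance of about 10% to 14%. A false claim of benefit has a chance of about 3% to 7% by normal theory (1.7% to 3.7% in simulation), against .025 per test. The two-sided tests, the any-one rule, the correlations, the over-dispersion and the mortality rates are all assumptions. The gap in the decision rule does not depend on them. It should be closed before the final data are analysed; Study duration forecasts data collection to November 2020, after the article's publication.

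**What to change.** Name time to first suicide-related re-presentation, compared by log-rank test at two-sided .05, as the single primary endpoint. This is the natural reading of the test already sized, since the Background gives .087 and .219 as re-attempt proportions. Test the re-presentation rate next at .05, only if the first test succeeds. Place all-cause mortality last in the sequence, or report it as an estimate with a confidence interval, because 75 intervention participants cannot be expected to show a significant mortality benefit at low death rates. Under this sequence family-wise error is at most .05.

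The abstract, Study aims, Study design and Primary outcomes need matching wording, and so does the registration if it carries the same three primaries. No further participants are needed and the first test loses no power, unlike a three-way Bonferroni split. The cost is that the rate and mortality results cannot be claimed as confirmatory if the first test fails, and that mortality loses its equal standing among the primary objectives. An alpha split or an all-three rule would also define the error rate, but the first needs a larger sample and the second is unlikely to be achievable.
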